## Abstract

**Background:**

After coronary artery bypass grafting (CABG), healthcare utilisation is high and is partly unplanned. eHealth applications have been proposed to reduce healthcare consumption and to enable patients to get actively involved in their recovery. This way, healthcare expenses can be reduced and the quality of care can be improved.

**Objectives:**

We aim to evaluate whether the use of an eHealth programme can reduce unplanned healthcare utilisation and improve mental and physical health in the first 6 weeks after discharge in patients who underwent CABG. In addition, patient satisfaction and use of the eHealth programme will be evaluated.

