## Introduction

Coronary artery bypass graft grafting (CABG) is the most prevalent cardiac surgery performed in the Netherlands, with roughly 7000 procedures annually [1]. The care chain of CABG is costly, and several quality improvement initiatives have been successfully implemented that sought to contain costs and to improve patient outcomes [2, 3]. Despite the positive effects of these initiatives on costs, mortality, postoperative morbidity and process measures such as in-hospital length of stay, healthcare utilisation in the first 30 days after CABG remains an issue, placing a significant burden on the healthcare system. Readmissions after CABG are commonly reported and the readmission rate can be as high as 34% in the first 30 days [4, 5].

Insight into unplanned healthcare utilisation during this period is scarce (apart from readmissions), but it is reasonable to expect a short hospital stay after CABG is counterbalanced by the use of other healthcare services, especially because planned care is not initiated until 6 weeks after discharge. In this period, patients commonly experience psychological symptoms (e.g. anxiety, depression), have to deal with uncertainty and worry about what to expect (e.g. what level of postoperative pain is normal, is physical exercise allowed?) [6]. Recall of information provided perioperatively is often incomplete and patients do not always know who to contact in case of complaints. They will then search for (sometimes unreliable) information on surgery or recovery and reach out to different healthcare providers, who have a varying degree of expertise in CABG care. Conflicting advice on recovery can further increase fear and insecurity, which will eventually hamper the recovery process and contribute to unplanned healthcare utilisation [7, 8].

We hypothesise that restructuring the postoperative period with an eHealth strategy will reduce unplanned healthcare utilisation through improved mental and physical health and faster recovery. In the IMPROV-ED trial, we aim to evaluate whether the use of an eHealth programme that consists of educational videos developed by the Dutch Heart Foundation (*Hartstichting*) and video consultations, is more effective than standard care in the reduction of unplanned healthcare utilisation and the improvement of patient outcomes in the first 6 weeks after CABG. In addition, a process and patient satisfaction evaluation of the newly developed eHealth strategy will be conducted.

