### Interventions

#### Control group

Patients randomised to the control group will receive standard care according to the local protocol. One month prior to surgery, patients are invited to the preoperative outpatient clinic, where they are individually counselled by a physician and a nurse practitioner. They are also handed information brochures after a nurse-led group session during which they receive information on the CABG care process at our hospital.

After surgery, patients have an in-hospital physiotherapist consultation. Before discharge, a resident or nurse provides brief information about the permitted level of physical activity and the medication schedules and answers remaining questions patients might have. Outpatient postoperative follow-up is scheduled for 6 weeks after discharge. Structured guidance to improve general condition and strength by a physiotherapist is offered (cardiac rehabilitation). Patients have no planned care in the first 6 weeks after discharge.

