### Outcomes

#### Primary outcome measure

The primary outcome is the volume of unplanned healthcare utilisation (resources used per patient). Healthcare utilisation is defined as a composite endpoint of all emergency department visits, outpatient clinic visits, rehospitalisation, patient-initiated telephone consultations with a physician or nurse, and visits to a general practitioner, allied health professionals and psychologists.

An adaptation of the Institute for Medical Technology Assessment Medical Consumption Questionnaire (iMCQ) will be used to determine the volume of healthcare utilisation and the reasons thereof. This generic questionnaire aims to determine the costs of healthcare based on care consumption and is applicable to the Dutch healthcare system [10]. The questionnaire answers will result in absolute frequencies of visits for the relevant care activities. When patients report the use of healthcare, their healthcare provider will be contacted to validate the date and the reason for the healthcare encounter. This information will be crossvalidated with the subjects’ self-reports.

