**Assessments**								
*Primary and secondary outcome measures*								
– Healthcare utilisation (iMCQ)						X		
*Tertiary outcome measures*								
– Quality of life (SF-36)	X							X
– Anxiety (HADS subscale)	X		X	X	X	X		
– Recovery (RI-10)			X	X	X	X		
*Process measures*								
– Patient satisfaction (satisfaction questionnaire)							X	
– Use of intervention (internet usage log)	X	X	X	X	X	X	X	X
*Patient and procedural data*								
– Sociodemographic data (iMCQ)	X							
– Patient characteristics (patient files)	X							
– Follow-up data (patient files)						X		

*iMCQ* Institute for Medical Technology Assessment Medical Consumption Questionnaire, *SF-36* 36-Item Short Form Health Survey, *HADS* Hospital Anxiety and Depression Scale, *RI-10* Recovery Index-10

^a^T_0_: 1 month before surgery; T_1_: 1 week after surgery; T_2_: 2 weeks after surgery; T_3_: 3 weeks after surgery; T_4_: 6 weeks after surgery; T_5_: 2 months after surgery; T_6_: 6 months after surgery

The SF-36 is routinely used at our facility and has been validated in multiple patient populations, including cardiac surgery patients [14–18]. This questionnaire assesses health-related quality of life in the previous 4 weeks. The HADS questionnaire is widely validated and is most commonly used to assess depression or anxiety. The RI-10 is a short, Dutch-language, 10-item questionnaire measuring postoperative domains on a 5-point scale over the last 7 days. It has been validated in gynaecology patients, but the general nature of the questions suits our patient population [19].

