### Data collection

Data will be collected using paper questionnaires at the following time points: 1 month before surgery (T_0_), 1 week after surgery (T_1_), 2 weeks after surgery (T_2_), 3 weeks after surgery (T_3_), 6 weeks after surgery (T_4_), 2 months after surgery (T_5_) and 6 months after surgery (T_6_) (Tab. 2). If patients do not return two subsequent questionnaires, they will be contacted and kindly requested to fill in and return the next questionnaires. Video consultation will be scheduled for 1 and 3 weeks after surgery.

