## Expected results

The IMPROV-ED trial will be carried out to evaluate whether an eHealth initiative consisting of online education and video consultation can reduce healthcare utilisation by improving quality of life, decreasing anxiety and accelerating recovery within the first 6 weeks after discharge for CABG.

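### The primary window is counted from discharge in some sections and from surgery in others, and the only utilisation questionnaire falls 6 weeks after surgery, before a discharge-based window closes

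*Protocol article*

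**What the plan says.** The protocol article gives the primary window in several places, and they do not agree.

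- **Counted from discharge.** The Abstract (Objectives) aims to "reduce unplanned healthcare utilisation and improve mental and physical health in the first 6 weeks after discharge". Expected results describes effects "within the first 6 weeks after discharge for CABG". The Control group section explains why this period matters: "Patients have no planned care in the first 6 weeks after discharge". It adds: "Outpatient postoperative follow-up is scheduled for 6 weeks after discharge".
- **Counted from surgery.** The Introduction states its aim as including "the improvement of patient outcomes in the first 6 weeks after CABG".
- **No window.** Under Primary outcome measure: "The primary outcome is the volume of unplanned healthcare utilisation (resources used per patient"). The composite is then listed without a start or end date.

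Measurement is tied to surgery. In Table 2 the row "Healthcare utilisation (iMCQ") is marked once, at T4. The table footnote and the Data collection section ("6 weeks after surgery (T_4") both count T4 from the operation. T5 carries satisfaction and T6 the SF-36; neither asks about utilisation. Providers are contacted to check date and reason only for encounters that the patient has reported.

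**The concern.** A window that opens at discharge and lasts 6 weeks cannot have closed when a questionnaire is completed 6 weeks after surgery, because the hospital stay lies between the two starting points. Read with the discharge anchor, the schedule stops observing the primary endpoint early, by a number of days that differs between patients. Later questionnaires do not fill the gap, and neither does provider validation, since it starts from the patient's report.

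Three things are at stake. The trial could report a result for 6 weeks after discharge that rests on a shorter period. Contacts late in the window would be lost. Raw counts per patient would also mix the rate of use with the time available for it, which adds variability to the comparison.

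**Working it through.** **Inputs.** From the protocol article: window of 6 weeks = 42 days; T4 at day 42 after surgery; one utilisation iMCQ; d = 0.35, α = 0.05, power 0.80 and total 260 (Sample size calculation). Length of stay is listed among the procedural characteristics to be collected, but no value is given, so L below is an assumption.

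**Step 1: the plan's own sample size.** Normal approximation, two-sided: n per arm = 2 × (1.960 + 0.842)² / 0.35² = 128.2, rounded up to 129, total 258. The two-sample t-test solution is 129.1, rounded up to 130 per arm, total 260. The stated figure reproduces. The effect size is not tied to a length of follow-up, so reconciling the window leaves it unchanged.

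**Step 2: days observed after discharge.** Observed days = 42 − L. Share of a 42-day discharge window lost = L / 42.

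| Assumed L (days) | Observed days | Share lost |
|---|---|---|
| 4 | 38 | 10% |
| 5 | 37 | 12% |
| 7 | 35 | 17% |
| 10 | 32 | 24% |
| 14 | 28 | 33% |

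The range 5 to 7 days is taken as the working case. The 14-day row shows what happens to an individual with a long stay; it is not offered as a typical value for elective, isolated CABG. Between a 4-day and a 14-day stay, exposure falls from 38 to 28 days (28/38 = 0.74, or 26% less).

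**Step 3: the surgery anchor.** If the window is 6 weeks from the operation, T4 closes it and nothing is lost at the end. The first L days are still spent in hospital, where a readmission or a visit to the general practitioner cannot arise. Time at risk after discharge is again 42 − L and again varies between patients.

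**Step 4: illustration of the cost in power.** Suppose that contacts accrue evenly in Poisson fashion, so that d shrinks with the square root of observed time, that d = 0.35 applied to the full 42 days, and that every patient has the same L. With 130 per arm, power = Φ(d × √((42 − L)/42) × √(130/2) − 1.96):

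- full window: about 0.81
- L = 5: 0.75
- L = 7: 0.73
- L = 14: 0.64

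The protocol states none of these assumptions, so the figures indicate scale only.

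**The case against.** The strongest reply is that the Introduction's wording fits T4 exactly, and that the outcome definition fixes no window, so the plan need not be read as setting a discharge window and then failing to measure it. That is fair. It turns the problem into a contradiction between sections, but does not remove it: the abstract, the Expected results and the rationale for the window all count from discharge.

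A reader might infer four stronger things that the document does not support.

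- **The treatment comparison is biased.** Allocation is randomised 1:1, so length of stay is balanced in expectation and both arms are cut short alike. Bias needs the programme to change length of stay. The videos are available before surgery, so this cannot be excluded, but nothing in the article says that they do so.
- **The scheduled outpatient visit will inflate the composite.** The endpoint is unplanned care and the reason for each reported encounter is validated, so that visit falls outside the definition. T4 as scheduled also precedes it.
- **Time at risk is ignored altogether.** Length of stay is recorded, collected data may be used to adjust endpoints, and a multivariate regression is planned. The Mann-Whitney comparison makes no such allowance, but the detail of the regression can properly sit in a document not shown here.
- **A large share of the data is lost.** The larger percentages come from assumed long stays.

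A late paper form might cover some of the missing days, and the recall wording of the adapted iMCQ is not shown. Any coverage gained by late return would be by chance. The one limit that later analysis cannot repair is that encounters after T4 are not asked about.

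**Conclusion.** The contradiction is real and concerns the primary endpoint. On the discharge anchor the last L days are unobserved by design: 12% to 17% of the window if stays are 5 to 7 days, an assumption because the article gives no figure. On either anchor, post-discharge time at risk is 42 − L days and varies by patient. The expected consequences are lost events, some added noise, and a conclusion worded for a longer period than was observed. The article gives no ground for concluding that the comparison is biased or that the sample size of 260 is wrong. The point should be fixed; it does not undermine the trial.

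**What to change.** Use one anchor for the window in the Abstract, Introduction, Primary outcome measure, Table 2, Data collection and Expected results.

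**Preferred.** Send the utilisation iMCQ 6 weeks after discharge, ask about contacts since discharge, and use the validated dates and reasons to count only unplanned encounters inside the window. T4 also carries the HADS anxiety subscale and the RI-10. If those stay tied to surgery, the iMCQ needs its own mailing. A form sent then arrives close to the scheduled outpatient visit, so the rule that planned visits do not count should be written down.

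**For patients already past T4, or if the mailing cannot move.** Enrolment began in February 2020, so this may apply. State the primary window as discharge to 6 weeks after surgery for all patients, and restrict patients followed before and after any change to that common window. Word the conclusion to match. Account for days at risk, derived from the recorded length of stay, in the planned regression or in a sensitivity analysis. A log-days offset belongs in a count regression; it cannot be added to the Mann-Whitney test, which can stay as the unadjusted comparison.

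**Cost.** Either one mailing moves by the length of stay, possibly as a separate form, or the stated window becomes slightly shorter. Both need a wording amendment. The sample size does not change.

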**Methods:**

For this single-centre randomised controlled trial, at least 280 patients referred for CABG will be included at the preoperative outpatient clinic and randomised to an intervention or control group. The intervention group will have access to an eHealth programme, which consists of online educational videos developed by the Dutch Heart Foundation and postoperative video consultations with a physician. The control group will receive standard care and will not have access to the eHealth programme. The primary endpoint is healthcare utilisation; other endpoints include anxiety, duration of recovery, quality of life and patient satisfaction. Participants will complete several questionnaires at 6 time points during the study.

**Results:**

Patient enrolment started in February 2020 and completion of the follow-up period is expected in August 2021.

**Conclusion:**

This randomised trial was initiated to test the hypothesis that patients who are partaking in our eHealth programme use less unplanned care and experience a better quality of life, less anxiety and a faster recovery than controls.

## Introduction

Coronary artery bypass graft grafting (CABG) is the most prevalent cardiac surgery performed in the Netherlands, with roughly 7000 procedures annually [1]. The care chain of CABG is costly, and several quality improvement initiatives have been successfully implemented that sought to contain costs and to improve patient outcomes [2, 3]. Despite the positive effects of these initiatives on costs, mortality, postoperative morbidity and process measures such as in-hospital length of stay, healthcare utilisation in the first 30 days after CABG remains an issue, placing a significant burden on the healthcare system. Readmissions after CABG are commonly reported and the readmission rate can be as high as 34% in the first 30 days [4, 5].

Insight into unplanned healthcare utilisation during this period is scarce (apart from readmissions), but it is reasonable to expect a short hospital stay after CABG is counterbalanced by the use of other healthcare services, especially because planned care is not initiated until 6 weeks after discharge. In this period, patients commonly experience psychological symptoms (e.g. anxiety, depression), have to deal with uncertainty and worry about what to expect (e.g. what level of postoperative pain is normal, is physical exercise allowed?) [6]. Recall of information provided perioperatively is often incomplete and patients do not always know who to contact in case of complaints. They will then search for (sometimes unreliable) information on surgery or recovery and reach out to different healthcare providers, who have a varying degree of expertise in CABG care. Conflicting advice on recovery can further increase fear and insecurity, which will eventually hamper the recovery process and contribute to unplanned healthcare utilisation [7, 8].

We hypothesise that restructuring the postoperative period with an eHealth strategy will reduce unplanned healthcare utilisation through improved mental and physical health and faster recovery. In the IMPROV-ED trial, we aim to evaluate whether the use of an eHealth programme that consists of educational videos developed by the Dutch Heart Foundation (*Hartstichting*) and video consultations, is more effective than standard care in the reduction of unplanned healthcare utilisation and the improvement of patient outcomes in the first 6 weeks after CABG. In addition, a process and patient satisfaction evaluation of the newly developed eHealth strategy will be conducted.

## Methods

### Study setting

This randomised trial is conducted at the Catharina Hospital in the Netherlands. The trial will be reported in accordance with relevant sections from the Standard Protocol Items: Recommendations for Interventional Trials [9], and the Consolidated Standards of Reporting Trials of Electronic and Mobile Health Applications and Online Telehealth. The study was approved by the local medical ethics committee (registration number R19.100) and is registered in the Netherlands Trial Registry (www.trialregister.nl, number NL8510).

### Recruitment and allocation

All patients planned for preoperative outpatient counselling for CABG will be contacted by telephone in the week of their scheduled appointment. Patient eligibility for the trial will be assessed according to prespecified inclusion criteria (Tab. 1). Eligible patients will be informed about the study protocol by one of the investigators after their scheduled appointment. If the patient is willing to participate, the informed consent form is signed. At inclusion, patients are randomised to either the intervention or control group in a ratio 1:1 using block randomisation, with a block size of four.

**Table 1 Tab1:** Eligibility criteria

Criterium	
1	>18 years of age planned for elective, isolated CABG/OPCAB
2	Sufficient computer knowledge, and internet access. Children can assist, but patients should be able to access their own email and navigate the internet to use the provided eHealth strategy
3	Access to computer with internet connection and webcam or build-in camera
4	Comply to minimal specifications for use of video consultation:
	– PC/laptop: Windows 7 or 10 with Chrome or Firefox browser
	– Android tablet: at least Nougat software installed and use of Chrome browser
	– Apple iPad: at least iOS 12.3.4
5	Ability to speak, read and interpret the Dutch language
6	Provide informed consent

*CABG/OPCAB* coronary artery bypass grafting/off-pump coronary bypass

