#### Intervention group

Aside from standard care as described in the previous section, patients in the intervention group will have access to educational videos and will be invited to two video consultations. Access will be granted through a link sent by email. The educational videos will be made available directly after randomisation for the duration of the study, via a secure online portal. The portal provides an orderly index in which patients can navigate by means of preformulated questions stratified in three categories: treatment, recovery and healthy living (Fig. 1). Each question will be accompanied by an educational video, which provides information and practical advice if applicable (Fig. 2).

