**Fig. 2 Fig2:**
[figure not shown]
Overview of the portal for the eHealth programme

The aim of the videos is to prepare patients, and their caregivers and family members for the surgery and offer guidance during the recovery process. The videos were developed by the Dutch Heart Foundation and were made available specifically for this study. Videos contain spoken text with animations (Figs. 3 and 4); all information is in Dutch. A nurse practitioner experienced in care for cardiothoracic surgery patients will conduct the video consultations with patients on their recovery and any complaints. Supervision will be provided by a cardiothoracic surgeon. The nurse practitioner will be told the study’s aim is to ‘improve the current follow-up procedure’ and that he or she will therefore be blinded for the specific outcomes.

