### Limitations

The addition of our eHealth strategy to the postoperative protocol might yield additional costs in comparison to standard care. We believe that these additional costs will be balanced by reduced healthcare utilisation and will therefore result in less total costs and better patient outcomes. Another potential limitation is that we will only include patients that have sufficient computer and digital literacy skills and have access to a computer or tablet, which might diminish generalisability of our study protocol. Moreover, as in most eHealth research, our trial is not fully blinded, which could lead to bias when patients report healthcare utilisation.

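### A single fixed block size of four, in a single-centre trial with visibly different arms, creates an avoidable risk that recruiters can foresee allocations

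*Protocol article*

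**What the plan says.** Under Recruitment and allocation, the protocol article says that "patients are randomised to either the intervention or control group in a ratio 1:1", "using block randomisation, with a block size of four". It gives one size only and mentions no stratification factor. The abstract confirms a single centre and the target: "For this single-centre randomised controlled trial, at least 280 patients referred for CABG will be included".

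On who recruits, the same section says: "Eligible patients will be informed about the study protocol by one of the investigators after their scheduled appointment". Consent is signed next, and randomisation takes place at inclusion. Table 1 makes eligibility depend in part on "Sufficient computer knowledge, and internet access".

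On visibility of the arms, the Intervention group section says: "The educational videos will be made available directly after randomisation for the duration of the study". Access comes through an emailed link, and controls receive none. The only staff blinding described is that of the nurse practitioner who runs the video consultations: "he or she will therefore be blinded for the specific outcomes". That blinding covers outcomes and not allocation. Under Limitations the article concedes that "our trial is not fully blinded, which could lead to bias when patients report healthcare utilisation". That sentence is about how patients report their care. It bears on allocation only in so far as it confirms incomplete masking.

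**The concern.** With one sequence and one known block size, past allocations carry information about the next one. Once two of the four places in a block have gone to the same arm, the rest of the block is fixed. A recruiter who can work this out knows the arm before approaching the patient, even if the list itself is well hidden.

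What is at stake is selection at entry. Whether a patient has enough computer knowledge is partly a judgement, and so is the way the trial is presented to a patient. If either shifts with the expected arm, even unintentionally, the groups may differ in digital ability, motivation or health before treatment starts. The analysis could adjust for recorded characteristics, but the article's list (age, sex, comorbidities, procedural and sociodemographic data) includes no measure of digital ability or motivation. Sociodemographic data would be a partial proxy at best.

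**Working it through.** **Inputs from the protocol article.** Block size 4, ratio 1:1, one centre, no stated stratification (Recruitment and allocation; abstract). Total 280, 140 per arm (Sample size calculation).

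**The plan's own figure.** The article gives no figure for predictability. Its sample size reproduces: a two-sided two-sample t-test with d = 0.35, α = 0.05 and power 0.80 needs 129.1, so 130 per arm, 2 × 130 = 260. The article raises this to 280. The block size does not affect that calculation. With N = 280 there are 280/4 = 70 blocks.

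**Assumption for what follows.** The recruiter knows the block size and every earlier allocation in order.

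**Determined positions.** A 1:1 block of four has 6 equally likely sequences: AABB, ABAB, ABBA, BAAB, BABA, BBAA.
- In AABB and BBAA, places 3 and 4 are determined: 2 × 2 = 4.
- In the other four, only place 4 is determined: 4 × 1 = 4.
- Total: 8 of 6 × 4 = 24 places, or 33.3%.
- Expected number of patients: 280 × 1/3 = 93.3. For 260 it is 86.7.

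**Best guess.** Always guess the arm with fewer patients so far in the block.
- Place 1: 1/2.
- Place 2: 2/3.
- Place 3: determined with probability 1/3, otherwise even, so 1/3 × 1 + 2/3 × 1/2 = 2/3.
- Place 4: 1.
- Average: (1/2 + 2/3 + 2/3 + 1)/4 = 17/24 = 70.8%, against 50% with no information.

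**Alternatives under the same full-knowledge assumption.** Fixed sizes are by exact enumeration. The mixes are by simulation (280 patients, 300 runs), with a recruiter who knows which sizes are in use but not their order.

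| Scheme | Certain in advance | Best guess correct |
|---|---|---|
| Fixed 4 | 33.3% | 70.8% |
| Fixed 6 | 25.0% | 68.3% |
| Fixed 8 | 20.0% | 66.6% |
| Random 4 or 6 | about 5.5% | about 69% |
| Random 4, 6 or 8 | about 2.1% | about 68% |

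With the 4/6/8 mix, 280 × 0.021 is about 6 patients, compared with about 93.

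**Could the video consultations reveal an open block?** Inclusion is about 1 month before surgery, and the earliest consultation the article mentions is 1 week after surgery, so about 5 weeks after randomisation. Enrolment began in February 2020 and follow-up was to end in August 2021. If that end includes the 6-month questionnaire, the last inclusion falls around January 2021, or about 48 to 52 weeks of accrual. At an even pace this is 280/52 = 5.4 to 280/48 = 5.8 patients a week, and a block of four fills in under a week. The consultations therefore come too late. Portal access, granted directly after randomisation, is the only route in the article that is early enough.

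**The case against.** The strongest objection is that the calculation rests on knowledge that the article does not attribute to recruiters. An investigator informs patients, but the article does not say that this person randomises, sends the links or sees earlier assignments. Its wording also leaves room for several recruiters, each of whom might know only part of the sequence. This objection stands: one third is a ceiling under full knowledge.

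The room to act on a prediction is also limited. All patients scheduled for preoperative counselling are telephoned, the criteria are prespecified, and most of the technical criteria are equipment checks. The computer-knowledge criterion is partly defined through use of email and the internet. This narrows the opening without closing it.

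Third, the gain from varying blocks is uneven, because best-guess accuracy falls only from 70.8% to about 68%. That is correct. The benefit lies mainly in removing near-certain knowledge of the next arm.

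A reader might infer that a third of allocations really were known to recruiters and that enrolment was steered. The document does not support this. It gives no evidence of steering, and the count of determined positions is not an estimate of bias in the outcome. A reader might also infer that concealment was lacking. A condensed article may leave list-holding and release after consent to the full protocol, so nothing is held against the plan on that score.

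**Conclusion.** The point holds as an avoidable risk of selection bias in a design parameter that the article fixes and makes public. Under full knowledge of the block size and the earlier allocations, one third of places (on average about 93 of 280) are determined in advance, and a best guess is right 70.8% of the time. With less knowledge both figures are lower. The calculation assumes a single unstratified sequence, as the text implies. Concealing the list would not by itself remove the risk if earlier allocations are known, because the next one can be deduced from them. The effect on the primary comparison cannot be quantified from the document.

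**What to change.** For patients not yet randomised, replace the fixed block of four with randomly varying block sizes, for example 4, 6 and 8, starting at a block boundary, and do not disclose the sizes to those who recruit. Report the change and its date.

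The cost is a regenerated list for the remaining patients. If recruitment stops inside a block of eight, the arms can differ by at most 4, which is negligible at 280. Sample size, endpoints and analysis stay as they are. The benefit reaches only patients still to be enrolled, who on the stated timeline may be few. If enrolment is already complete, the report can state the block size and say whether those who recruited had access to earlier allocations, so that readers can judge the risk.
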